### Eligibility criteria {10}

Participants must meet at randomisation all the inclusion criteria and none of the exclusion criteria listed in Table 1.

**Table 1 Tab1:** Inclusion and exclusion criteria

Inclusion criteria	Exclusion criteria
• Being diagnosed with T2DM; • Aged ≥ 18 and ≤ 85 years old; • Having an HbA1c level > 7% (53 mmol/mol) and < 12% (108 mmol/mol); • Being able to walk without walking aids; • Having provided written informed consent; • Having a smartphone or a tablet and being able to download the App that will be used to insert the required data	• Having a BMI < 18 kg/m^2^ and > 45 kg/m^2^; • Having a sBP < 100 or > 200 mmHg and/or dBP < 50 or > 120 mmHg; • Being diagnosed with a stage 5 CKD^a^ • Being diagnosed with a NYHA stage IV; • Poor collaboration (i.e. unwilling to modify the actual plan of control and therapy, even if not ideal) for which adherence to the study is unlikely • Having no possibility of using a smartphone or a tablet • Having medical conditions affecting the study participation (i.e. life expectancy < 1 year)

*Abbreviations*: *BMI* body mass index, *CKD* chronic kidney disease, *dBP* diastolic BP, *HbA1c* glycated haemoglobin type A1c, *NYHA* New York Heart Association, *T2DM* type 2 diabetes mellitus, *sBP* systolic BP

^a^based on the glomerular filtration rate according to the CKD-Epidemiology Collaboration equation < 15 ml/min/m^2^ accounting for individual body surface [20]

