#### Secondary outcome measures

Secondary outcome measures are collected at different time point (for specific times of data collection refer to Table 4).Proportion of participants with Hb1Ac < 53 mmol/mol within the two arms;Difference in HbA1c levels between the two arms other than at 12 months;Reporting frequency and number of new hypoglycaemic episodes within the two arms;Proportion of participants reaching the targeted lipid profile (LDL level < 70 mg/dl and non-HLD cholesterol level < 100 mg/dl) and BP levels (sBP < 130 mmHg or > 140 if ≥ 65 years old);Effect on weight, lipid profile and BP levels for the App users;Effect on physical activity performed during the last 7 days prior filling in the questionnaire, for both arm participants;Number of hospitalisation events within the two arms;Number of measurements and level of physical activity with the prescribed activities (body weight monitoring, BP measurements, physical activity) within the two arms;Changes in quality of life (QoL) scores for participants of both arms;Satisfaction and usability score of the App in the intervention arm;

**Table 4 Tab4:** Time schedule of enrolment, interventions and assessments during the study period, adapted from the example template provided by the SPIRIT Group [28]

	Enrolment		Allocation		Post-allocation			Close-out	Personnel and participant involvement	Method of data collection
Timepoint	14 to 21 days prior T0	7 to 14 days prior T0	0 months	0 months (T0)	3 months (T1) (± 30 days)	6 months (T2) (± 30 days)	9 months (T3) (± 30 days)	12 months (T4) (± 30 days)		
ENROLLMENT										
** Informal study information**	x	x							Clinician	Scheduled appointment at clinic
** Eligibility screen**	x	x							Clinician or PI	Scheduled appointment at clinic
** Informed consent signed**		x							Clinician or PI and participant	Face-to-face meeting
** Allocation**			x						Research team	Face-to-face meeting
** Blood tests prescription**		x							Clinician	Face-to-face meeting
** Provide 3 copies of IPAQ questionnaire**		x							Research team	Face-to-face meeting
INTERVENTION										
** App education and instruction manual**				x					Research team	Face to face meeting
** Inform GP of participation**				x					Clinician	Through email
** Help and support with the App use**				x	x	x	x	x	Research team	Phone- email
** App (intervention) monitoring**				x	x	x	x	x	Clinician or research team	Medical dashboard

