** Medical intervention via App – data recording**				x	x	x	x	x	Clinician and participant	Medical dashboard
ASSESSMENTS: clinical and biohumoral variables and clinical indicators										
** Body weight and number of checks (previous month)**		x			x	x	x	x	Research team	Face to face meeting, medical dashboard /App or other recording tools
** Vital signs and number of checks (previous month)**		x			x	x	x	x	Research team	Face to face meeting, medical dashboard/App or other recording tools
** Demographic characteristics and clinical variables**^**a**^		x							Clinician and research team	Face to face meeting, HIS
** Hb1Ac levels and number of checks**		x			x	x	x	x	Clinician, research team, laboratory personnel	HIS
** Other blood tests**^**b**^		x						x	Clinician, research team, laboratory personnel	HIS
** Questionnaires (SF-12/MMAS-4/DASI)**				x				x	Research team, participant	Face to face meeting
** IPAQ questionnaire**				x	x	x	x	x	Research team, participant	Face to face meeting and phone call
** SUS questionnaire (App group only)**								x	Research team, participant	Face-to-face meeting
** Number of nursing and medical (tele)consultation and chat interactions**					x	x	x	x	Research team	Medical dashboard/App and HIS
** Number of unscheduled specialists visits (macro- and micro-vascular complications), number of accesses to ED for cardiac, cardiovascular or diabetic problems**					x	x	x	x	Research team	HIS
** Number of therapeutic plan changes**					x	x	x	x	Research team	Medical dashboard/App and HIS
** Time spent for (tele)consultation**						x			Research team	Recording of time during visit
** Number of hospitalisation**						x	x	x	Research team	HIS
** Number of hypoglycaemic episodes**					x	x	x	x	Research team, participants	Medical dashboard/App and/or download of data from glucometer

*Abbreviations*: *DASI* Duke Activity Status Index, *ED* emergency department, *HbA1c* Glycosylated Haemoglobin Type A1C, *HIS* Hospital Information System, *IPAQ* International Physical Activity Questionnaire, *MMSA-4* Morisky Medication Adherence Scale, *SF-12* Short Form-12, *SUS* System Usability Scale, *PI* Principal Investigator

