### Who will be blinded {17a}

Given the nature of the intervention, which is the active use of the Smartphone App, it will not be possible to guarantee the blindness of participants, healthcare staff and the person responsible for data collection. Vital signs, body weight and height are recorded before randomisation by a trained nurse across sites, using standardised procedures and instruments. The blood tests’ analysis will be carried out within the Trusts according to standardised procedures. Laboratory personnel are not involved in the study, thus they are not aware of the participants’ allocation. Blindness is guaranteed during data analysis, as data analysis will be performed from assessors that are not directly involved in the study. Filled-in questionnaires will only report the unique randomisation number.

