## Statistical methods

### Analysis primary and secondary endpoints {20a}

The analyses of the primary and secondary endpoints will be performed based on the intention-to-treat and as per-protocol approaches. Continuous variables of the two groups will be presented as mean, SD and quartiles, whilst categorical variables will be presented as percentages.

The normality of the distributions is determined by using the normality test of Kolmogorov–Smirnov. To compare the differences between the two groups for continuous outcomes, Student’s *T* test will be used. If the assumption of normality of data distribution does not hold, Wilcoxon’s rank sum test will be used. For repeated measures of continuous variables for which there is an assumption of normality of data distribution, the one-way ANOVA test will be used. If the assumption of normality does not hold, the Friedman test will be used instead of the one-way ANOVA test.

Chi-squared test will be used for categorical outcomes. SAS 9.4 (SAS Institute Inc.) will be used to conduct analyses. For all tests, the significance level is set to 0.05 (2-sided). Professional statisticians ([name]) will conduct all analyses.

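### Adjusting the secondary BP-target and lipid-target comparisons for entry status and centre would add precision at almost no cost; the planned chi-squared test is valid but leaves baseline data unused

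*Protocol article*

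**What the plan says.** The secondary outcome list in section {12} includes "Proportion of participants reaching the targeted lipid profile (LDL level < 70 mg/dl and non-HLD cholesterol level < 100 mg/dl) and BP levels", the BP part being "BP levels (sBP < 130 mmHg or > 140 if ≥ 65 years old". It does not say how someone already at target at entry is classified. Section {20a} gives one method for outcomes of this kind: "Chi-squared test will be used for categorical outcomes". No baseline covariate or stratum is named.

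On entry, Table 1 requires "Having an HbA1c level > 7% (53 mmol/mol) and < 12% (108 mmol/mol", so everyone starts above the HbA1c target. For BP it excludes only "Having a sBP < 100 or > 200 mmHg and/or dBP < 50 or > 120 mmHg", and it has no lipid criterion. Section {16a} stratifies randomisation by centre alone.

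The baseline data are collected. Section {17a} says "Vital signs, body weight and height are recorded before randomisation by a trained nurse across sites", and Table 4 with its footnote b schedules the lipid panel before T0 and again at 12 months.

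**The concern.** A person with systolic BP of 120 mmHg, or with both lipid values already below their limits, can enrol. Such a person is much more likely to be at target at 12 months than someone who starts off target. An unadjusted test treats that predictable variation as noise. If one arm happens to start with more people at target, part of that gap carries straight into the 12-month difference, in either direction.

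At stake is the precision of the comparison behind the secondary objective on BP and cholesterol control. The trial is sized for HbA1c only, so precision on these outcomes is limited to begin with.

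**Working it through.** **The plan's own figure.** The protocol gives no sample size or power for target attainment. Its HbA1c figure reproduces: (3² + 7²) × (1.96 + 0.8416)² / 3² = 58 × 7.849 / 9 = 50.6, so 51 per arm and 102 in total. With 120 randomised and 20% drop-out, 120 × 0.8 / 2 = 48 per arm complete. I use n = 48.

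**Assumed inputs (the documents give none).** b = share at target at entry; a = share of these still at target at 12 months, equal in both arms; c and t = share reaching target among those off target, control and App. Central case: b = 0.4, a = 0.8, c = 0.2, t = 0.4.

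**Precision, central case.**
- Arm proportions: control 0.4 × 0.8 + 0.6 × 0.2 = 0.44; App 0.4 × 0.8 + 0.6 × 0.4 = 0.56; difference 12 points.
- Unadjusted variance: (0.44 × 0.56 + 0.56 × 0.44) / 48 = 0.4928 / 48 = 0.01027.
- Variance stratified by entry status: [b × 2a(1−a) + (1−b)(c(1−c) + t(1−t))] / n = (0.4 × 0.32 + 0.6 × 0.40) / 48 = 0.368 / 48 = 0.00767.
- Ratio 0.368 / 0.4928 = 0.747, equivalent to 1 / 0.747 − 1 = 34% more participants.
- Power (two-sided 5%, normal approximation): Φ(0.12 / 0.1013 − 1.96) = 22% unadjusted; Φ(0.12 / 0.0876 − 1.96) = 28% stratified.

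**Varying b, other inputs central.**

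| b | Difference (points) | Variance ratio | Power, unadjusted | Power, stratified |
|---|---|---|---|---|
| 5% | 19 | 0.94 | 53% | 55% |
| 10% | 18 | 0.89 | 47% | 51% |
| 30% | 14 | 0.77 | 29% | 35% |
| 40% | 12 | 0.75 | 22% | 28% |
| 50% | 10 | 0.73 | 17% | 21% |

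Five scenarios within b = 30-50%, a = 70-85%, c = 15-25% and t = c + 20 points gave variance ratios of 0.64-0.87, a cut of 13-36%. The extreme corners of that grid give 0.62 and 0.89.

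**Chance imbalance.** The SD of the between-arm difference in entry status is √(2b(1−b)/n). At b = 0.4 this is √(0.48 / 48) = 10 points. A 10-point imbalance moves the 12-month difference by (a − c) × 10 = 0.6 × 10 = 6 points before any App effect. By exact binomial calculation for b = 30-50%, an imbalance of 10 points or more occurs in 32-36% of trials at 48 per arm, 23-28% at 51 and 27-32% at 60. The figures are uneven because 10 points means a gap of 5 people at 48 and 6 at 51 or 60.

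**Type I error.** Simulation with no App effect (51 per arm, a = 0.85, c = t = 0.2, b = 0.2, 0.4 and 0.6; 40,000 runs each) gave 4.9-5.8% for chi-squared and 4.8-5.1% for the stratified test. Among only those trials with an imbalance of 10 points or more, chi-squared rejected in about 14-15% and the stratified test in 4.5-5.3%.

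**Dilution.** The overall difference is b × (App minus control among those at target) + (1−b) × (t − c). In the central case this is 0.4 × 0 + 0.6 × 20 = 12 points, identical to the crude difference. Stratifying narrows the interval but does not enlarge the effect.

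**The case against.** An unadjusted chi-squared test on a secondary binary outcome in a randomised trial is valid, and the case made here is the general case for baseline adjustment. A separate analysis plan, not shown, might add it. Both are fair. They limit the point to precision and conditional protection, but they do not remove it, because the protocol does name a test and that test cannot use entry status.

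Three stronger readings are tempting, and the documents support none of them.
- A reader might infer that the test is wrong or biased. It is not: unconditional size stays near 5%, and the 14-15% applies only to the subset of trials with a marked imbalance.
- A reader might blame the test for dilution. The dilution comes from the outcome definition, as the identical 12-point differences show.
- A reader might say that people already at target carry no information about the App. That assumes it cannot help them stay there, whereas the secondary objective concerns control. If 70% of controls and 85% of App users stayed at target, other central inputs unchanged, the difference would be 0.4 × 15 + 0.6 × 20 = 18 points, against 20 with nobody at target at entry.

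The choice of b also matters. Nothing in the protocol supports 30-50% for the lipid target, which requires two limits together. If few people meet it at entry, the gain there is small.

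**Conclusion.** The point holds as a cheap improvement in precision, and in protection against chance imbalance, for two secondary proportions. The protocol has the baseline data and names a test that does not use them. The HbA1c target proportion raises no such issue of people already at target, because everyone enters above that target.

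The size is conditional on assumptions throughout: a variance cut of roughly 13-36% if 30-50% are at target at entry, and two to four points of power if 5-10% are. Even after adjustment, power in the central case is only 28%, so these outcomes remain imprecise. No error in the trial's validity follows.

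**What to change.** In section {20a}, analyse 12-month BP-target and lipid-target status by logistic regression on arm, centre and baseline values: systolic BP and age group for the BP target, LDL and non-HDL cholesterol for the lipid target. Report the standardised risk difference with its 95% confidence interval. A Cochran-Mantel-Haenszel test stratified by baseline target status and centre is an acceptable alternative, and the safer one if too few reach the lipid target to fit the model. Keep the chi-squared result as supporting.

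Because adjustment leaves the dilution in place, also report descriptively, by arm, the proportion newly reaching target among those off target at entry and the proportion remaining at target among those already there.

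Before anyone is classified, reconcile the systolic BP threshold for participants aged 65 or over, which runs in opposite directions in the secondary outcome list and in Table 3.

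The cost is a sentence in the methods and an extra table row, with no new data, visits or participants. The downside is a model-based estimate in place of a test on raw percentages.

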### Interim analyses {21b}

No interim analysis is planned. The study will stop in case the targeted sample size is not reached within the end of the funded initiative (Telemechron project is expected to end in late 2023) despite all efforts have been put in place to recruit participants. No harm is expected, and therefore, there are no other reasons why the study should be prematurely stopped.

### Methods for additional analyses (e.g. subgroup analyses) {20b}

No subgroup analyses were planned.

### Methods in analysis to handle protocol non-adherence and any statistical methods to handle missing data {20c}

The analysis will be conducted by “intention to treat” and “per protocol”. Given our expectation that very few patients will crossover or be lost to follow-up, these analyses should agree very closely.

Missing data will be managed according to the SAS version 9.3 MI procedure, which consists of the multiple imputation methods chosen by pattern of data missingness and type of imputed variable (SAS Institute Inc.)

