### Sample size {14}

The sample size was calculated on the basis of the primary hypothesis (Hb1Ac levels are likely to decrease more in the subjects of the intervention group than for the subjects of the control group at 12 months). A lower variability around the HbA1c mean level is also expected for the subjects in the intervention group when compared to the HbA1c mean level for the subjects in the control group. It was assumed that at 12 months, the mean Hb1Ac level will be 49 (SD ± 3) mmol/mol in the intervention group and 52 (SD ± 7) mmol/mol in the control group. In order to achieve a power of 80% and to keep the significance level at 5%, the sample size was calculated to be 102 (51 in each group) by using Open Epi (a freely accessible software, https://www.openepi.com/Menu/OE_Menu.htm) as depicted in Fig. 1 below. Assuming 20% of drop-out, the required sample was calculated as 120.

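### The normality gate and multiple imputation do not combine into one pre-specified primary test: the gate can choose Student's t in some imputed data sets and Wilcoxon in others

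*Protocol article*

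**What the plan says.** Section {20a} of the protocol article names Student's t as the default comparison of the two arms for continuous outcomes, which include the primary endpoint, HbA1c at 12 months. Whether it is used depends on the data: "The normality of the distributions is determined by using the normality test of Kolmogorov–Smirnov". If the check fails, the test changes: "If the assumption of normality of data distribution does not hold, Wilcoxon’s rank sum test will be used". Repeated measures follow the same pattern, with one-way ANOVA giving way to Friedman. Proportions are not gated: "Chi-squared test will be used for categorical outcomes".

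Section {20c} says "Missing data will be managed according to the SAS version 9.3 MI procedure", described as "multiple imputation methods chosen by pattern of data missingness and type of imputed variable".

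On the amount of missing data, section {14} says "Assuming 20% of drop-out, the required sample was calculated as 120", while {20c} expects little loss to follow-up.

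**The concern.** Section {20a} is written for a single data set: check normality, then choose the test. Section {20c} produces several completed data sets, and the normality check can come out differently in each. Pooling rules combine the same quantity across data sets. They do not combine a difference in means from some sets with a rank-sum statistic from others.

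If the sets disagree, someone must decide after seeing them whether to overrule the gate, run it only on the observed values, or choose one test. The primary result then rests on a choice that the plan did not make. This is separate from whether a normality gate is wise with complete data.

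**Working it through.** **1. The plan's own figures (section {14}).** Means 49 and 52 mmol/mol (difference 3), SDs 3 and 7, 80% power, two-sided 5%.

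n per arm = (3² + 7²) × (1.960 + 0.842)² / 3² = 58 × 7.849 / 9 = 50.6, rounded up to 51, or 102 in total. This reproduces the plan. With 120 recruited, a 20% loss means 120 × 0.20 = 24 missing values, about 12 per arm.

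**2. What pooling needs.** Rubin's rules take an estimate Q and a variance U from each of M imputed sets. The pooled estimate is the mean of the Qs, and its variance is T = mean(U) + (1 + 1/M) × B, where B is the variance of the Qs across sets. Q must be the same quantity in every set.
- Student's t supplies a mean difference and its standard error, so it pools directly.
- The Wilcoxon z can be pooled by the same formula with U = 1. A chi-squared statistic can be pooled by the D2 rule, and Friedman's statistic could be too (not simulated).
- A mixture of t and Wilcoxon across sets has no common Q.

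**3. How often the gate disagrees with itself.** All runs assume 60 per arm and imputation by normal regression on baseline HbA1c. The gate is rerun in every imputed set.

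| Setting | Loss | Trials in which the gate chose different tests |
|---|---|---|
| 10 imputations, Lilliefors form in either arm, log-SD 0 / 0.10 / 0.15 / 0.20; 250 trials each | 20% | 33% / 42% / 50% / 56% |
| 20 imputations, gate on residuals, common SD 5, correlation with baseline 0.5, normal / gamma-skewed; 2,000 trials each | 20% | 28% / 72% |
| 20 imputations, SDs 3 and 7, correlation 0.5, normal / log-scale skew 0.3 / 0.5; 1,000 trials each | 20% | 45% / 78% / 47% |
| As the row above | 5% | 25% / 42% / 12% |

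A further check with 20 imputations, correlation 0.5, 20% loss and 800 trials per setting gave 44% to 77%.

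**4. Type I error when one test is fixed and pooled.** Null trials, settings of the second row, normal / skewed, nominal 5%:
- t by Rubin's rules: 5.6% / 4.1%
- Wilcoxon z by Rubin's rules: 5.7% / 4.3%
- chi-squared by D2: 4.1% / 3.0%

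The Monte Carlo standard error is √(0.05 × 0.95 / 2000) = 0.5 points.

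**5. Running the gate once, on observed values, then pooling the chosen test.** In null trials this gave 4.5% and 5.1% (normal data) and 4.9% and 4.6% (log-SD 0.20). With section {14}'s SDs of 3 and 7 and assumed skewed data, the picture changes:

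| | Rejections at equal means | Power at a difference of 3 |
|---|---|---|
| Gate on observed data, chosen test pooled | 7% to 17% | 63% to 69% |
| Mean difference, Rubin-pooled | about 5% | 81% to 83% |

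The reason is that with right skew the median lies below the mean, and further below in the arm with the wider spread, here control. A rank test therefore sees a difference when the means are equal, and it loses part of a true difference that favours the intervention.

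**The case against.** The strongest reply is that the two sections do not contradict each other. The article does not say that the gate is rerun in each imputed set. Run once on the observed values, it cannot disagree with itself, and step 5 shows error near 5% in ordinary settings. The pooling rule, the imputation model and the number of imputations are commonly left to an analysis plan, which is not shown here. Missing data may also be scarcer than 20%: section {14} gives a sample-size allowance, {20c} expects little loss, and {18b} lets the team collect clinical outcomes from hospital records for participants who do not complete. The simulations impute from baseline alone, although Table 4 schedules HbA1c at 3, 6 and 9 months.

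Much of this stands. The absence of a pooling rule is not a fault in an article, and the disagreement rates would fall with fewer losses or better predictors. What does not fall away is that the rule for choosing the primary test is stated, and stated for one data set. An analysis plan would have to restrict, override or drop it. Restricting it to observed values removes the disagreement but leaves the loss shown in step 5 under the trial's own SDs if the data are skewed.

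A reader might infer that multiple imputation cannot be carried through the named tests at all, or that type I error is too high. The documents support neither. The default t test pools directly, and the pooled Wilcoxon and chi-squared tests kept their error in step 4. Type I error of 7% to 10% arises if one imputed set is tested by Wilcoxon as if it had been observed, and the plan does not say to do that.

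**Conclusion.** The point holds for the choice of test. As printed, the plan does not fix one primary intention-to-treat test, because a data-driven gate is paired with several imputed data sets. At an assumed 20% loss the gate split across sets in roughly 30% to 75% of simulated trials. At 5% loss the range was 12% to 42%. These rates measure how often the plan gives no single answer; they are not error rates.

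The benefit of changing the rule depends on the data. It is small if HbA1c is near normal or the arms have equal spread. It is material if the data are skewed and the SDs differ as section {14} assumes. The results rest on 60 per arm, values missing at random or completely at random, imputation from baseline only, and assumed shapes of the HbA1c distribution, none of which beyond the sample size and SDs comes from the article.

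**What to change.** In section {20a}, drop the normality gate for the primary endpoint. Pre-specify the arm difference in mean 12-month HbA1c from a linear model in each imputed set, with a standard error that allows unequal variances (section {14} assumes SDs of 3 and 7), combined by Rubin's rules. For proportions, use a logistic or binomial regression arm effect combined in the same way.

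In section {20c}, state that imputation is done by arm and includes baseline and the 3-, 6- and 9-month HbA1c. Keep the rank tests as a labelled sensitivity analysis.

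The cost is a rewording of two sections and a few lines of SAS (PROC MIANALYZE). No new data are needed. The rank tests lose their confirmatory role, and some power is lost if the data prove strongly skewed with equal spread in the two arms.
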